### Project Phases and Study Design

3.1

Each phase of the project will use different quasi‐experimental designs. Table 1 presents a summary of the study design, population, setting, variables, sample size, and study period for each phase.

**TABLE 1 fsn371640-tbl-0001:** Study designs, study populations, study settings, study variables, sample size and estimated study periods for each phase of the project.

	Project phases			
	Phase 1	Phase 2	Phase 3	Phase 4
Study design	Three‐arm pre‐post parallel design	Four‐arm placebo‐controlled single‐blind pre‐post parallel design	Four‐arm placebo‐controlled single‐blind pre‐post parallel design	Two‐arm placebo‐controlled, single‐blind (participants), parallel feasibility trial
Study population	Healthy‐weight adults living in Australia	Healthy‐weight adults living in Australia	Overweight or Obese adults living in Australia	Overweight or Obese adults living in Australia
Study setting	Laboratory‐based	Laboratory‐based	Laboratory‐based	In a natural environment (at home)
Independent variable	Different MB doses (175, 350, and 700 mg)	Different MB doses (175, 350, and 700 mg) and placebo	Different MB doses (175, 350, and 700 mg) and placebo	MB or Placebo consumption in a natural environment
Dependent variable	Sour, bitter, tart, and sweet taste perception ratings of food‐based solutions and individual food items	Ratings for sourness and bitterness taste perceptions, overall liking and intake of hypo‐palatable mixed vegetarian salad Ratings for sweetness taste perceptions and overall liking of SSBs	As mentioned in Phase 2	Primary outcomes Food preferences (Overall meal liking and preferences across time) Energy intake Dietary quality Other outcomes of interest Feasibility of the treatment protocol and study procedures Appetite Anthropometry/Body composition
Sample size	54	40	40	30
Proposed study period	1 July–30 September, 2024	1 November 2024–30 September 2025	1 December–30 June, 2025	1 May–30 December, 2025

*Note:* Sociodemographic characteristics (sex*, age, income, employment status, and education status), phenotypic taste perception, genotypic taste sensitivity, mouth pH, anthropometry, and body composition will be collected as covariates. In Phases 3 and 4, comorbidities (e.g., diabetes, hypertension) and medication use (self‐reported) will also be assessed. In Phase 4, physical activity will be measured as a covariate for secondary outcomes. *Sex is classified based on biological characteristics.

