*Note:* For non‐acidic solutions and food items (bitter and tart), we planned to use the solutions mixed with citric acid, as an acidic pH was essential for the taste modification action of miraculin (Doddawad et al. 2022). Food samples were kept in a refrigerator, then removed and placed on separate plastic trays 10 min before each test.

First, sociodemographic characteristics and anthropometric measurements will be collected. Saliva samples will then be obtained for TAS2R38 genotyping, and oral pH and phenotypic taste sensitivity will be assessed. As illustrated in Figure 1, participants (*N* = 54) will subsequently be allocated into three groups (*n* = 18 per group). Prior to commencing the pre‐test session, participants will be instructed to drink a sip of water and wait at least 30 s (Choi and Garza 2020). In their respective groups, participants will receive 10 mL of each solution and pieces of single food items to rate their perceived taste perception on a generalized labeled magnitude scale (gLMS). Participants will rinse their mouths with water between each solution or food item until the previous taste stimulus is gone (Igarashi et al. 2013; Lipatova and Campolattaro 2016).

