**FIGURE 1 fsn371640-fig-0001:**
[figure not shown]
Phase 1 study design.

After the pre‐test, participants will drink water to neutralize their mouths. Group A will receive 175 mg (half a tablet), Group B will receive 350 mg (one tablet), and Group C will receive 700 mg (two tablets) doses in MB tablets. Subjects will be instructed to dissolve the tablet with saliva on their tongue for 5 min and make contact with the tablet against as much surface area of the oral cavity as possible without chewing or swallowing it (Hudson et al. 2018). Immediately after dissolving, participants will receive the same solutions and food items used for the pre‐test to capture changes in perceived taste perception on gLMS.

#### Phase 2

3.7.3

A hypo‐palatable vegetarian salad containing half‐serve vegetables (raw broccoli and rocket leaves) and half‐serve fruits (Granny Smith apple), which are the minimum possible servings per Australian dietary guidelines (Brownie et al. 2015), will be prepared 30 min before the data collection time at Griffith University, Gold Coast campus kitchen lab or the Participants' home, based on the participants' preferences. Food items for the vegetarian salad and the Coca‐Cola (representing hyper‐palatable SSB) will be purchased from the local market. The food will be stored in a refrigerator (4°C), removed, and placed on separate plastic trays 10 min before each test. The SSB will be kept at room temperature, and 30 mL will be poured into 50 mL paper cups, which are clean and uniform in color (Mielby et al. 2018).

Figure 2 shows that participants (*n* = 40) will be allocated to four treatment arms (*n* = 10 in each group). The data collection procedure will follow these steps:

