Initially, participants will review the participant information sheet and screening questions and sign a consent form. They will confirm (tick) the standardized instructions provided before their visit.Anthropometry measurements and body composition assessments will be conducted, and eligibility will be confirmed.For the TAS2R38 gene, saliva will be collected using the Oragene DNA OG‐500 kit as mentioned in Table 3.The pH of the mouth will be measured using a pH paper strip as mentioned in Table 3.Phenotypic taste sensitivity will be assessed by having participants place a PTC strip on the tip of their tongues.Rate their hunger level using the 10‐point hunger scale (0 = full, and 10 = very hungry), and assess their current mood status using a 10‐point mood scale (0 = happiness, and 10 = sadness).After rinsing their mouths with water, participants will receive a weighted vegetarian mixed salad. They will consume as much or as little from the given salad.Participants will rate the sourness and bitterness taste perception of the salad using gLMS, followed by their overall liking of the salad using the Labeled Affective Magnitude Scale (LAMS). The principal investigator will measure and record any leftover salad to measure their intake.After rinsing their mouths with water, participants will drink 30 mL of regular Coca‐Cola and rate its sweetness‐taste perception on gLMS and overall liking on LAMS.Participants will be required to wait for a compulsory 20‐min period after the pre‐testing procedures before commencing post‐testing. This interval is intended to allow hunger levels to return to baseline. The duration is based on the estimated energy content of the test meal (60 kcal, i.e., 251 kJ). Drawing on Horner et al. (2014), whose participants required approximately 3 h to recover from a ~1600 kJ meal, we calculated that ~23 min would be sufficient for our test meal; therefore, a minimum 20‐min waiting period will be adopted. As this duration may not fully account for individual differences in metabolism, dietary fiber intake, or the amount consumed during the pre‐test, participants will be verbally informed of the rationale for the interval and asked to notify the investigator once their hunger has returned to baseline. They will then be asked to complete the same hunger scale used upon arrival at the lab. If post‐waiting hunger ratings are comparable to baseline, the post‐test will proceed; otherwise, the waiting period will be extended until hunger levels return to baseline.According to their assigned group, participants will rinse their mouths and dissolve a given dose of MB (175, 350, 700 mg) or placebo (350 mg) in their mouth for 5 min.A vegetarian salad similar in content and amount to the one provided in the pre‐test will be provided. Participants will consume it as desired, and the principal investigator will measure and record any leftovers.Participants will rate the sourness and bitterness taste perception of the salad using gLMS, followed by their overall liking using LAMS.Finally, participants will rinse their mouths with water, drink 30 mL of regular Coca‐Cola, and rate the sweetness taste perception using gLMS and their overall liking using LAMS.

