##### Second Visit (End of Baseline Week)

3.7.5.2

In this visit, the 3‐day food record sheet provided in the first visit will be collected from study participants. Then, participants (*n* = 30) will be allocated into two arms. Then, participants will be given the required number of tablets (MB or placebo) in their respective groups for 6 weeks. Moreover, they will be provided with a 3‐day food record sheet and requested to complete it in the last week of this follow‐up period, before the third. Instructions will be provided to encourage participants to use a minimum amount of lime or lime juice while they administer tablets (to activate miraculin) with their meals in their daily lives. However, unlike the lab phases, no other strict standardization procedures will be imposed, as the aim is to evaluate the feasibility and acceptability of MB use in everyday dietary contexts.

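### Phase 1 allocates to dose groups before the pre-test with no blinding stated, and Phases 2–3 do not fix when allocation happens; the arm should be opened only after the pre-test

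*Protocol article*

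**What the plan says.** **Phase 1 (section 3.7.2).** Sociodemographic data, anthropometry, saliva, oral pH and PTC sensitivity come first. Participants "will subsequently be allocated into three groups". The pre-test follows: "In their respective groups, participants will receive 10 mL of each solution and pieces of single food items" and rate them on the gLMS. After the pre-test the tablets are given: "Group A will receive 175 mg (half a tablet), Group B will receive 350 mg (one tablet"), with two tablets (700 mg) for Group C. Table 1 describes this phase as a "Three‐arm pre‐post parallel design"; in the same row the other three phases carry a single-blind label.

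**Phases 2 and 3 (sections 3.7.3 and 3.7.4).** The paragraph before the numbered procedure refers to Figure 2 and says that the 40 participants "will be allocated to four treatment arms". The first listed step is "Initially, participants will review the participant information sheet and screening questions and sign a consent form". Eligibility confirmation, baseline tests, salad and cola ratings, a wait of at least 20 minutes and a repeat hunger rating follow. If hunger is comparable to baseline the post-test goes ahead; "otherwise, the waiting period will be extended until hunger levels return to baseline". The assigned group is first used in the next step, when the tablet is dissolved. Phase 3 uses the same procedure. Table 1 calls both phases single-blind without saying who is blinded; only the Phase 4 entry adds that it is the participants.

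**Phase 4 (section 3.7.5.2).** Baseline questionnaires and measurements are taken at the first visit. At the second, "In this visit, the 3‐day food record sheet provided in the first visit will be collected from study participants", and allocation to the two arms comes after that.

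**The concern.** The pre-test supplies half of every pre-post comparison. If the person running it, or the person rating, knows the dose group, the way instructions are given or ratings are made can differ by arm before any tablet is taken. Such a difference looks like a dose effect and cannot be separated from one afterwards.

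The risk matters more here because other protection is thin. The designs are described as quasi-experimental (section 3.1), no randomisation or concealment is described for Phases 1–3, the Phase 1 outcomes are self-rated, and the Phase 1 doses differ visibly in tablet count.

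In Phases 2–3 there is a second possible opening. The wait can be prolonged on a criterion with no stated tolerance, and hunger at the second salad test could influence intake. Whether the arm is known at that moment depends on when allocation occurs, which the text leaves open.

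**Working it through.** **Order of events, by phase**

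| | Phase 1 | Phases 2–3 | Phase 4 |
|---|---|---|---|
| Allocation relative to baseline outcome measures | Before, explicitly | Not fixed; mentioned before the step list, not a step | After, explicitly |
| First use of the arm | Tablet, after pre-test (the pre-test is also described as run within groups) | Tablet, after pre-test and hunger re-rating | Tablets handed out at visit 2 |
| Blinding in Table 1 | None stated | Single-blind, party not named | Single-blind, participants |
| Hunger check and extendable wait | None | Yes | None |

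1. In Phase 1 the sequence needs no inference. Solutions and foods at the pre-test are the same for all groups, so the assignment serves no purpose until the tablet is given.
2. In Phases 2–3 the allocation sentence cannot be read as a time stamp. Taken as chronology it would put allocation before consent and eligibility, the first two steps. The step list shows only that the arm exists by dosing.
3. Phase 4 shows that allocation after baseline measurement is already part of this project's practice.

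**What an arm-specific shift would do (illustration)**

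The protocol has no figure to reproduce on this point. Inputs: 18 per group in Phase 1 and 10 per group in Phases 2–3 (sections 3.7.2 and 3.7.3), and two-sided 5% significance. The shift δ, in SD units of the change score, is an assumption; 0.25 and 0.5 are shown as a range.

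For a two-group t-test on change with no true effect, the noncentrality is δ / √(2/n) with 2n − 2 degrees of freedom. The rejection probability is P(|T| > critical t).

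| n per arm | df | critical t | δ | noncentrality | rejection probability |
|---|---|---|---|---|---|
| 10 | 18 | 2.101 | 0.25 | 0.25/√0.2 = 0.559 | 8.3% |
| 10 | 18 | 2.101 | 0.5 | 0.5/√0.2 = 1.118 | 18.5% |
| 18 | 34 | 2.032 | 0.25 | 0.25/√(1/9) = 0.75 | 11.3% |
| 18 | 34 | 2.032 | 0.5 | 0.5/√(1/9) = 1.5 | 30.8% |

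This treats the comparison as a difference in change, where the shift enters in full. Table 6 specifies a mixed model with dose, time and a participant effect. If dose entered only as a main effect averaged over two balanced time points, the shift would enter at half its size, (δ + 0)/2.

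**The case against.** The route to a biased pre-test is narrow. Taste, liking and hunger are rated by the participant, every arm gets the same pre-test items, tablets come later, and nothing says that participants are told their dose in advance. In Phases 2–3 intake is weighed. The shifts used above have no source in the protocol. An article may also leave assignment logistics to a fuller document, and Figures 1 and 2 were not available in the text reviewed. These points limit the likely size of the problem. They do not remove the Phase 1 ordering, which the article itself prescribes.

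A reader might infer that all three laboratory phases allocate before the pre-test and the hunger check, and that an unblinded investigator decides how long each arm waits. The documents do not support this:

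- Phase 1 has no hunger check and no waiting rule, so the phase with explicit early allocation is not the phase with the extendable wait.
- For Phases 2–3, early allocation rests only on paragraph order.
- An unblinded investigator is a natural reading of single-blind, by analogy with Phase 4, but it is not stated for Phases 2–3.
- The participant notifies the investigator and re-rates hunger; nobody is named as judge of whether the ratings are comparable.

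The missing tolerance for that judgement is a separate matter, and reordering allocation would not supply it.

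Finally, Table 1 schedules Phase 1 for July to September 2024, so its procedure may no longer be changeable.

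**Conclusion.** The point holds for Phase 1 as written: the pre-test is taken after assignment, within dose groups, with no blinding stated and no reason given. For Phases 2–3 the finding is that the timing of allocation is not fixed in the procedure, while the design is only single-blind and the wait depends on an undefined criterion. Early knowledge of the arm is possible there but not documented.

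The protocol does not allow the bias to be sized. The rejection probabilities of about 8% (10 per arm) and 11% (18 per arm) rest wholly on the assumed 0.25 SD shift and on a change-score comparison. They show sensitivity to such a shift, not that one will occur. The case for acting is that the better order is nearly free and closes the route entirely for the pre-test values.

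**What to change.** - **Section 3.7.2:** move allocation to after the last pre-test rating, immediately before the tablet is given, and delete the wording that places the pre-test within groups.
- **Sections 3.7.3 and 3.7.4:** add allocation as a listed step, after the post-wait hunger rating has been recorded and the decision to proceed made. The assignment is opened immediately before the tablet is given. If this is already the practice, one sentence saying so is enough.
- **Table 1:** state who is blinded in Phases 2–3, and state that Phase 1 is open if it is.
- **If Phase 1 has been completed:** report when allocation took place and who knew the group during the pre-test.

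The cost is one reordered step and a few words. Sample size, measurements and analysis are unchanged.

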**FIGURE 1 fsn371640-fig-0001:**
[figure not shown]
Phase 1 study design.

After the pre‐test, participants will drink water to neutralize their mouths. Group A will receive 175 mg (half a tablet), Group B will receive 350 mg (one tablet), and Group C will receive 700 mg (two tablets) doses in MB tablets. Subjects will be instructed to dissolve the tablet with saliva on their tongue for 5 min and make contact with the tablet against as much surface area of the oral cavity as possible without chewing or swallowing it (Hudson et al. 2018). Immediately after dissolving, participants will receive the same solutions and food items used for the pre‐test to capture changes in perceived taste perception on gLMS.

#### Phase 2

3.7.3

A hypo‐palatable vegetarian salad containing half‐serve vegetables (raw broccoli and rocket leaves) and half‐serve fruits (Granny Smith apple), which are the minimum possible servings per Australian dietary guidelines (Brownie et al. 2015), will be prepared 30 min before the data collection time at Griffith University, Gold Coast campus kitchen lab or the Participants' home, based on the participants' preferences. Food items for the vegetarian salad and the Coca‐Cola (representing hyper‐palatable SSB) will be purchased from the local market. The food will be stored in a refrigerator (4°C), removed, and placed on separate plastic trays 10 min before each test. The SSB will be kept at room temperature, and 30 mL will be poured into 50 mL paper cups, which are clean and uniform in color (Mielby et al. 2018).

Figure 2 shows that participants (*n* = 40) will be allocated to four treatment arms (*n* = 10 in each group). The data collection procedure will follow these steps:
Initially, participants will review the participant information sheet and screening questions and sign a consent form. They will confirm (tick) the standardized instructions provided before their visit.Anthropometry measurements and body composition assessments will be conducted, and eligibility will be confirmed.For the TAS2R38 gene, saliva will be collected using the Oragene DNA OG‐500 kit as mentioned in Table 3.The pH of the mouth will be measured using a pH paper strip as mentioned in Table 3.Phenotypic taste sensitivity will be assessed by having participants place a PTC strip on the tip of their tongues.Rate their hunger level using the 10‐point hunger scale (0 = full, and 10 = very hungry), and assess their current mood status using a 10‐point mood scale (0 = happiness, and 10 = sadness).After rinsing their mouths with water, participants will receive a weighted vegetarian mixed salad. They will consume as much or as little from the given salad.Participants will rate the sourness and bitterness taste perception of the salad using gLMS, followed by their overall liking of the salad using the Labeled Affective Magnitude Scale (LAMS). The principal investigator will measure and record any leftover salad to measure their intake.After rinsing their mouths with water, participants will drink 30 mL of regular Coca‐Cola and rate its sweetness‐taste perception on gLMS and overall liking on LAMS.Participants will be required to wait for a compulsory 20‐min period after the pre‐testing procedures before commencing post‐testing. This interval is intended to allow hunger levels to return to baseline. The duration is based on the estimated energy content of the test meal (60 kcal, i.e., 251 kJ). Drawing on Horner et al. (2014), whose participants required approximately 3 h to recover from a ~1600 kJ meal, we calculated that ~23 min would be sufficient for our test meal; therefore, a minimum 20‐min waiting period will be adopted. As this duration may not fully account for individual differences in metabolism, dietary fiber intake, or the amount consumed during the pre‐test, participants will be verbally informed of the rationale for the interval and asked to notify the investigator once their hunger has returned to baseline. They will then be asked to complete the same hunger scale used upon arrival at the lab. If post‐waiting hunger ratings are comparable to baseline, the post‐test will proceed; otherwise, the waiting period will be extended until hunger levels return to baseline.According to their assigned group, participants will rinse their mouths and dissolve a given dose of MB (175, 350, 700 mg) or placebo (350 mg) in their mouth for 5 min.A vegetarian salad similar in content and amount to the one provided in the pre‐test will be provided. Participants will consume it as desired, and the principal investigator will measure and record any leftovers.Participants will rate the sourness and bitterness taste perception of the salad using gLMS, followed by their overall liking using LAMS.Finally, participants will rinse their mouths with water, drink 30 mL of regular Coca‐Cola, and rate the sweetness taste perception using gLMS and their overall liking using LAMS.

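### The 23-minute waiting time in Phases 2 and 3 does not follow from its printed inputs, which give about 28 minutes, and the adopted 20-minute minimum is below both

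*Protocol article*

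**What the plan says.** The step list in Section 3.7.3 (Phase 2) of the protocol article asks participants to "wait for a compulsory 20‐min period after the pre‐testing procedures before commencing post‐testing", so that hunger can return to its starting level. The derivation is given in full. It starts from the meal: "The duration is based on the estimated energy content of the test meal (60 kcal, i.e., 251 kJ". It takes its reference from a cited study, "whose participants required approximately 3 h to recover from a ~1600 kJ meal". From these it concludes "we calculated that ~23 min would be sufficient for our test meal", and goes straight on to the rule: "therefore, a minimum 20‐min waiting period will be adopted".

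The same step admits that a fixed time may not suit everyone, and mentions the amount eaten at the pre-test as one reason. Participants therefore repeat the hunger scale after the wait. If the rating is comparable to the first one, the post-test proceeds; "otherwise, the waiting period will be extended until hunger levels return to baseline". The tablet is then dissolved in the mouth for 5 minutes before the second salad is served.

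Section 3.7.4 states that Phase 3 follows the same procedures. Table 1 lists intake and overall liking of the salad among the dependent variables of Phase 2 and refers Phase 3 back to Phase 2.

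**The concern.** The article prints both inputs and result, and they do not agree. The result is then used to justify a procedural rule in two phases with 40 participants each. The direction is also unfavourable: a time described as sufficient is followed by a minimum that is shorter than it.

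Salad intake and liking are measured twice in one session, and the wait is there to keep the first salad from influencing the second. If some fullness remained, it would tend to lower intake and perhaps liking at the second test, against the increase that the investigators hope to see. The planned mixed model has time (pre-post) as a within-subject factor, so a shift of this kind would enter the pre-post change within each arm.

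**Working it through.** **Inputs (all from Section 3.7.3)**
- Test meal: 60 kcal, printed as 251 kJ. Check: 60 × 4.184 = 251.04 kJ, so the conversion is right.
- Reference meal: about 1600 kJ.
- Reference recovery time: about 3 h = 180 min.
- Stated result: about 23 min. Adopted minimum: 20 min.
- Tablet step between the wait and the second salad: 5 min.

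**Attempt to reproduce the stated figure.** The article names no scaling rule. The natural one is proportional to energy:

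time = reference time × test-meal energy / reference-meal energy = 180 × 251/1600 = 28.2 min.

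The stated 23 min is not reproduced: 23/28.24 = 0.81, about 19% too low. Working in kcal changes nothing, because the ratio is the same.

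**What would give 23 minutes?** One input at a time would have to be:
- reference meal: 180 × 251/23 = 1964 kJ (printed: about 1600);
- reference time: 23 × 1600/251 = 147 min, or 2.4 h (printed: about 3 h);
- test meal: 23 × 1600/180 = 204 kJ, or 49 kcal (printed: 251 kJ, 60 kcal).

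**Can rounding explain it?** With 3 h and a reference meal of 1550 to 1650 kJ, the result is 29.2 to 27.4 min. Only a reference time of about 2.5 h comes near: 150 × 251/1600 = 23.5 min. That is a large departure from the printed 3 h. Square-root scaling gives 180 × √(251/1600) = 71 min, further away.

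**How much is uncovered, on proportional scaling?**

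| Time after the pre-test | Share of 28.24 min | Energy covered | Energy uncovered |
|---|---|---|---|
| 20 min (end of the minimum wait) | 70.8% | 20 × 1600/180 = 178 kJ | 73 kJ (29.2%) |
| 25 min (after the 5-min tablet step) | 88.5% | 25 × 1600/180 = 222 kJ | 29 kJ (11.5%) |

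The second row is the relevant one for intake, because the second salad is served only after the tablet has dissolved. The gap at that point is 28.2 − 25 = 3.2 min. It assumes that the full 251 kJ was eaten. A participant who ate less than about 89% of it (222/251) is fully covered at 25 min on the same scaling.

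**The case against.** The strongest reply is that the 20 minutes is only a floor and that the hunger rating is the operative rule. If the rating has not returned to its starting level, the wait is extended; if it has, the purpose of the wait is met, however the floor was derived. The article also concedes that a fixed time will not fit everyone and gives that as the reason for the check. This largely stands. What it leaves open is that the article sets no tolerance for a comparable rating. Participants are also told why they are waiting and asked to say when they are ready. The floor is thus the only fixed element, and its derivation is wrong.

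A second reply is that the real interval between salads is longer than 25 minutes. The ratings, rinse and cola follow the first salad before the wait begins, and the hunger scale and another rinse come after it. No durations are given, but if these steps add about 3.2 minutes, the salad-to-salad interval already reaches 28.2. This is fair, and it is why 11.5% is an upper figure.

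A third reply is that the inputs are approximate and linear recovery is an assumption. That limits the precision of the kJ figures, but does not rescue the 23 minutes, which the article presents as calculated from these inputs.

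**Conclusion.** The arithmetic slip is real. The printed inputs give about 28 minutes, the article states about 23, and the adopted minimum of 20 is below both. This rests on proportional scaling, the obvious reading of inputs given as one energy, one reference energy and one time.

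The practical size is small: at most about 11.5% (29 kJ) of the meal uncovered at the second salad, if the full 251 kJ was eaten, recovery is linear, and no other step takes any time. If the 60 kcal leaves out the 30 mL of cola drunk before the wait, that energy comes on top; the article does not say.

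Two stronger readings are tempting and are not supported. A reader might infer that almost 30% of the meal is still uncovered at the second salad; that share belongs to the end of the 20-minute wait and ignores the tablet step. A reader might also infer that residual fullness depresses the post-test results in every arm, or biases the active tablet against placebo. Nothing in the article shows that fullness remains once the hunger rating has returned to baseline. All arms share the same waiting rule, so carry-over does not by itself bias the comparison with placebo. What remains at risk is mainly the within-arm pre-post change in intake and liking.

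**What to change.** Reconcile the five figures in Section 3.7.3: 251 kJ, 1600 kJ, 3 h, 23 min and 20 min. If the inputs are as printed and scaling is proportional, correct the calculated time to about 28 minutes and base the minimum pre-to-post interval on it. If an input is misprinted or another scaling rule was used, correct or state that instead. Say whether the 5-minute tablet step counts towards the interval, and whether the 60 kcal includes the cola. Keep the hunger check; a numeric tolerance for a comparable rating would make it firmer. The same text then serves Phase 3.

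No change to the analysis model is needed. In particular, pre-test intake should not be added as a covariate, because it is already a response in the planned pre-post mixed model.

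The cost is a short correction of the text and a few minutes more per session: about 3 if the tablet step counts (28.2 − 25), about 8 if it does not (28.2 − 20). For sessions already held under the 20-minute rule, the report can give the derivation correctly and describe the interval that was used.
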